## Abstract

The management of tibial pilon fractures is challenging and often leads to complications and limitations in ankle function. The study aims to investigate myotonometric parameters and muscle strength of ankle muscles, as well as gait pattern and balance among patients following surgical treatment of pilon fractures. The randomized controlled study will analyze the differences between the patients who will follow a 3-month physical exercise program and will wear customized foot orthoses (i.e., customized orthotic arch support insoles) versus patients who will attend only the physical exercise program. For each group, at least 21 patients will be required. The assessment involves four different testing procedures: myotonometry (anterior tibialis, medial and lateral gastrocnemius, and longus peroneus assessed using MyotonPRO), muscle strength testing (ankle dorsiflexors, plantar flexors, and peroneal muscles assessed using MicroFET2 dynamometer), analysis of gait parameters (using Scheinworks treadmill), and double-leg and single-leg balance tests (using K-Force plate). After 3 months, the assessments will record which of the two treatments (physical exercise program with or without wearing customized foot orthoses) has better outcomes in regaining ankle muscle properties and tone, as well as the restoration of gait and balance.

## 1. Introduction

Pilon fractures are not very common, leading to increased rates of complications and poor clinical outcomes especially in terms of walking impairments [1,2,3]. Various methods of stabilizing pilon fractures are used in clinical practice. Treatment usually consists of open reduction and internal fixation or limited internal fixation combined with an external fixator. These types of fractures are mostly caused by high-energy trauma; they are frequently associated with soft tissue injuries requiring repeated surgery for definitive management and generating thus additional costs, as well as long recovery periods [2,4]. In many cases, the functionality of the affected ankle or leg is not fully regained, severely affecting lifestyle among those affected [5,6,7,8]. There are various publications in the literature that discuss treatment techniques for pilon fractures and evaluate their clinical, functional, and radiological outcomes [1,2,3,4,5]. After sustaining a tibial pilon fracture, individuals may experience long-term complications that impact their quality of life. This is especially true for comminuted intra-articular fractures caused by high-energy trauma. Studies have shown that patients with tibial pilon fractures have lower scores on health-related quality of life questionnaires than uninjured age-matched populations and even people with chronic diseases like AIDS, diabetes, or asthma [5,6]. Patients who underwent surgery for this type of fracture also report a notable loss of ankle joint function and the presence of daily pain. Returning to work may be difficult for these patients, with only 57% of them returning to professional activities after 12 months [5]. Additionally, posttraumatic arthrosis is a common complication of tibial pilon fractures. Studies have revealed that clinical outcomes can worsen with the passage of time. In a study conducted by Chen et al. [9], patients who have undergone open reduction and internal fixation treatment for severe tibial pilon fractures experienced a significantly higher incidence of posttraumatic arthrosis after 2 years, which further increased at the final evaluation (averaging 10 years). Patients with more severe soft tissue injuries at the time of presentation had poorer clinical outcomes [7]. Moreover, the adequacy of reduction was found to be a predictor for long-term outcomes [5].

Gait parameter analysis is a commonly used method to evaluate the functional performance in various populations [10,11,12]. However, only a few studies have analyzed gait parameters after tibial pilon fractures, which are crucial indicators of the effectiveness of the surgical treatment [13,14,15,16]. When compared to healthy controls, patients with pilon fracture who needed surgery and immobilization present altered gait patterns and clinical symptoms [13,14]. Similar to other studies [7,14], in our study, the non-injured ankle on the opposite side will serve as the healthy control. Soft tissue injuries, prolonged immobilization, and extended periods of non-weight-bearing activity on the injured side resulting from tibial pilon fractures can lead to muscle atrophy, decreased strength, and stiffness [17,18]. Pilon fractures can also lead to balance disturbances [19]. The altered balance can greatly impact walking and functional mobility, thus limiting daily activities and reducing the overall quality of life [19,20,21]. Better understanding of the gait parameters and leg muscle properties alteration after pilon fracture surgery could improve therapeutic procedures. It is important to note that successful treatment should result in improved joint mobility, restored muscle strength, and reduced pain and swelling, that ultimately lead to normalized gait parameters and optimal functioning in everyday and sport recreational activities [12,22,23,24,25,26,27]. According to a systematic review, people who performed active exercises after ankle surgery were able to return earlier to daily activities and work [28]. The use of orthotics is a frequently used practice for various neurological and musculoskeletal conditions for improvement in functional mobility and increased quality of life [15,29,30]. The foot orthoses are used to regain walking ability, correct foot deformities, and maintain the stability of lower limb joints. Customized orthotic design promotes patient rehabilitation, especially in restoring natural gait patterns [31]. To our knowledge, analysis of gait parameters, balance, and muscle assessment before and after rehabilitation has not yet been performed among patients with surgically treated pilon fractures. In our study, we hypothesize that patients with unilateral pilon fractures will have improved gait parameters, balance, muscle strength, and functional parameters after following a 3-month exercise program and wearing foot orthoses. The parameters of the affected ankle should be similar to those of the contralateral non-injured ankle.

### Study Objectives

This study aims to conduct a comprehensive assessment of the muscles and gait parameters in patients who have undergone surgery for pilon fractures and compare the results before and after a physical exercise training program with or without wearing foot orthoses represented by customized orthotic arch support insoles. The purpose of our study is to investigate whether combining foot orthoses with an exercise program leads to improved gait parameters, balance, and ankle muscle properties compared to the exercise program alone.

## 2. Materials and Methods

This protocol was developed in accordance with the SPIRIT guidelines [32] and describes an outcome-assessor-blinded, two-arm, parallel-group, randomized controlled trial. Subjects will be randomly allocated (using a system of random number tables by one investigator who will not be involved in the recruitment process and data collection) into either the group that will wear foot orthoses in addition to physical exercise (Group 1) or the group that will only perform physical exercise training (Group 2). The investigators who are involved in data analysis, baseline, and follow-up assessments will be blinded to group allocation.

### 2.1. Sample Size Calculation

The sample size was calculated using G*Power 3.1.9.7 (Heinrich-Heine-Universität, Düsseldorf, Germany), with a significance level of 0.05, 0.8 power, and an effect size of 0.8. A total of 42 subjects will participate in the study (21 per group) [33].

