## 5. Conclusions

The randomized controlled study aims to provide options for the long-term management of treatment for patients that have followed surgery for tibial pilon fractures. After 3 months, the assessments will record which of the two therapeutic alternatives (physical exercise program with or without wearing customized foot orthoses) achieves better outcomes in what concern the regain of ankle muscle properties and tone, as well as the restoration of gait and balance.

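### The 21 per group in Section 2.1 gives 0.8 power only for a one-sided unadjusted t-test; two-sided power is 0.716, and the article does not say how the baseline values enter the between-arm comparison

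*Protocol article*

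**What the plan says.** Section 2.1 names G*Power and gives its inputs: "with a significance level of 0.05, 0.8 power, and an effect size of 0.8". The result is 42 patients, 21 per group. It names no test family, sidedness, outcome, covariate or correlation.

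The question across arms is stated in several places. Study Objectives says the trial will "compare the results before and after a physical exercise training program with or without wearing foot orthoses", and its next sentence asks whether adding orthoses to exercise does better than exercise alone. The Abstract and the Discussion state the same contrast. Conclusions says "After 3 months, the assessments will record which of the two therapeutic alternatives" achieves the better outcomes.

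The opening of Section 2 shows that outcomes are assessed twice and masked: investigators doing the analysis, "baseline, and follow-up assessments will be blinded to group allocation". Section 2.2.4 forms the two groups before the baseline assessment. Section 3 (Expected Results) declines to say which group will do better on myotonometry, strength or balance.

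**The concern.** Two things in the stated plan do not sit well together. The sample size meets its own target only under a one-sided test, while the authors say they have no expectation about direction for three of the four outcome families. A reader who assumes the usual two-sided 5% test will believe the trial has 0.8 power when it has about 0.72.

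The trial also collects the data that could recover most or all of that shortfall, namely a baseline value of every outcome, and does not say how they will be used. The wording in Study Objectives and Conclusions leaves room for three analyses: raw 3-month values, before/after changes, or 3-month values adjusted for baseline. They differ materially in power at 21 per arm. The change score can be worse than ignoring baseline altogether.

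**Working it through.** **Inputs from Section 2.1.** Alpha 0.05, power 0.8, effect size d = 0.8, n = 21 per group. I read d as a difference in means divided by the SD of the 3-month value.

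**Assumed, because the article gives no figure.** The baseline to 3-month correlation rho (0.2 to 0.7 shown), equal SDs at the two times, and no dropout.

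**Step 1: reproduce the plan's figure.** Two-sample t-test, noncentral t with df = 2n − 2 and noncentrality d·√(n/2).
- n = 21: noncentrality 0.8 × √10.5 = 2.592, df = 40.
- One-sided 5%, critical value 1.684: power 0.817. With n = 20 it is 0.799, so 21 is the smallest n that reaches 0.8. The plan's figure is reproduced exactly.

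**Step 2: the same calculation two-sided.**
- n = 21, critical value 2.021: power 0.716.
- Smallest n reaching 0.8: 26 per group, 52 in total. The plan's 42 is not reproduced.

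**Step 3: the three ways to compare arms.** Each replaces d in the noncentrality by an effective value.
- Raw 3-month value: d, df = 40.
- Change score: d / √(2(1 − rho)), df = 40. At rho = 0.5 the variance factor is 2 × 0.5 = 1, the same as the raw value. Below 0.5 it exceeds 1, so the change score is worse.
- ANCOVA: d / √[(1 − rho²)(1 + 1/(2n − 4))], df = 39. The second factor, 1 + 1/38, is the small-sample cost of estimating the baseline slope. At rho = 0.5: 0.8 / √(0.75 × 1.0263) = 0.912.

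Two-sided 5%, 21 per group:

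| rho | Raw 3-month | Change score | ANCOVA | ANCOVA minus raw |
|---|---|---|---|---|
| 0.2 | 0.716 | 0.516 | 0.721 | 0.005 |
| 0.3 | 0.716 | 0.571 | 0.744 | 0.028 |
| 0.4 | 0.716 | 0.637 | 0.777 | 0.061 |
| 0.5 | 0.716 | 0.716 | 0.822 | 0.106 |
| 0.6 | 0.716 | 0.807 | 0.877 | 0.161 |
| 0.7 | 0.716 | 0.904 | 0.937 | 0.221 |

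ANCOVA is at least as good as both alternatives in every row, so the direction of the advice does not depend on rho; its size does. Power reaches 0.8 at rho of about 0.45 (0.798 at 0.45, 0.802 at 0.46). Leaving out the small-sample factor gives 0.831 instead of 0.822 at rho = 0.5; the lower figure is the safer one to quote. If the test is one-sided, ANCOVA at rho = 0.5 raises power from 0.817 to 0.896.

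**Step 4: chance baseline difference.** Its SD is √(2/21) = 0.31 baseline SDs, so a difference above 0.5 SD arises in about 1 trial in 10. At rho = 0.5 such a difference moves the raw 3-month contrast by 0.5 × 0.5 = 0.25 SD in that trial.

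**The case against.** The strongest reply is that the article commits to no analysis model, and that a model is normally fixed in a full protocol or SAP, neither of which is shown. This stands in part. A reader might infer from the before/after wording and the covariate-free sample size that an unadjusted or change-score analysis is planned and that about 10 points of power are lost. The documents do not support that. Those sentences say what is asked and when it is measured, and ANCOVA fits them. Sizing without a covariate is a common conservative choice. The 10 points also hold only near rho = 0.5. Nor is the trial described only as a before/after comparison, since the Abstract, Study Objectives, Discussion and Conclusions all state the between-arm contrast.

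Second, a one-sided test could be intended: Study Objectives asks whether adding orthoses improves outcomes. If so, the stated power is met. But sidedness is not given, and Section 3 disclaims a direction for myotonometry, strength and balance.

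Third, the 0.8 may already be on a change or adjusted scale, because Section 2.1 names no outcome. Then the ANCOVA gains do not apply on top of it, although the two-sided shortfall in Step 2 remains.

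Fourth, a reader might take the chance baseline difference in Step 4 as bias, or take allocation without described stratification as a fault. Neither follows. Under randomisation the unadjusted estimate is unbiased and its test keeps its error rate. The cost is precision.

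Last, Section 2.2.4 allocates before baseline, so the covariate is measured after allocation. That is acceptable if treatment cannot have affected it. The blinded baseline assessors in Section 2 and barefoot gait testing in Section 2.4.1 point that way, but the condition should be written down.

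**Conclusion.** The point holds in a limited form. It is certain that 21 per group matches the stated inputs only as a one-sided unadjusted t-test, if a two-sample t-test with d = 0.8 was used. Two-sided power is then 0.716, a shortfall of 0.8 − 0.716 = 0.084 against the stated target. It is also clear that the article does not say how the baseline values enter the between-arm comparison.

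What adjustment would gain is conditional. For rho from 0.3 to 0.6 it adds roughly 3 to 16 points two-sided and brings power to between 0.74 and 0.88. It restores 0.8 only if rho is about 0.45 or more. At lower correlations 42 patients remain short of 0.8 even with adjustment. These figures assume 0.8 on the 3-month SD, equal SDs and no dropout. No loss of power has been shown to be built into the plan. This is a change that should be made, not an error that invalidates the design.

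**What to change.** In Section 2.1:
- State that the test is two-sided at 0.05.
- State that the between-arm comparison of each outcome is an ANCOVA of the injured limb's 3-month value on randomised group and the same measure's baseline value. Use the patient-level value where a measure has no side, such as cadence.
- Restate the power with its assumptions: 21 per group and effect size 0.8 on the 3-month SD give 0.74, 0.78, 0.82 and 0.88 for rho 0.3, 0.4, 0.5 and 0.6, against 0.716 unadjusted. Label rho as assumed, and say that about 0.45 is needed for 0.8.

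In Study Objectives, say that before/after changes within each arm are descriptive.

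In Section 2.2.4, where groups are formed before baseline, add that the baseline covariate is measured barefoot, by assessors blinded to allocation, before any insole is worn.

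The cost is wording only. The baseline values are already collected, so no visit, measurement or patient is added. Each model uses one more degree of freedom, which the figures above already include.

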### 2.2. Recruitment and Informed Consent

This study includes patients who underwent surgical treatment for tibial pilon fractures. Prior to the study, patients will be presented with both verbal and written information regarding the study. They will then be required to provide written consent. The study is conducted in accordance with the Declaration of Helsinki. The study was approved by the Ethics Committee of the Victor Babes University of Medicine and Pharmacy Timisoara (reference no. 26/2023-08-25) and it was registered in the Iranian Registry of Clinical Trials on 28 August 2023 (reference no. IRCT20230813059137N1).

#### 2.2.1. Eligibility Criteria

The following are the requirements for participation in this study: patients must be adults who have undergone surgery for unilateral tibial pilon fracture; they must show clinical and radiological evidence of fracture healing; they must be able to apply full weight bearing onto the affected leg; they must agree to participate voluntarily. In addition, it is necessary for them to have a healthy contralateral lower limb that can be used as a healthy control (Figure 1).

#### 2.2.2. Exclusion Criteria

Individuals will be excluded from the study if they have a history of traumas or fractures in the affected lower limb, a history of traumas or fractures in the opposite lower limb (used as healthy control), any neurological or other health conditions that may cause difficulty in walking or changes in muscle function, or lower leg asymmetry not related to the tibial pilon fracture. Patients with psychiatric disorders or severe cardiovascular disease, morbid obesity (BMI > 40), or cancers will be excluded from the study due to the potential of these conditions to affect compliance and limit the follow-up [34].

#### 2.2.3. Discontinuing Criteria

Any patients who do not use the foot orthosis or fail to comply with the exercise program will be excluded from the study. Also, patients who, during the rehabilitation period, suffer any lower limb injury or any injury that may affect gait or muscle strength will be excluded from the study.

#### 2.2.4. Interventions

Before the baseline assessment, patients will be divided into two groups. Both groups will undergo an identical exercise program. Group 1 will also wear carbon foot orthoses with full reinforcement specially designed to correct the asymmetries detected on the first set of measurements. Gait parameters analysis can help determine specific movement asymmetries [12,13,14]. The Scheinworks treadmill will be used for this purpose, allowing a practical equilateral overview of important gait parameters [35]. During the analysis, the following parameters were taken into consideration: maximum force exerted by the forefoot and backfoot (expressed as a percentage in relation to body weight); step length (measured in centimeters), which is the distance between the foot contacts on opposite sides of the body; stance phase (expressed as a percentage), which is the period of the gait cycle when the foot is in contact with the ground; swing phase (also expressed as a percentage), which is the period of the gait cycle when the foot is not in contact with the ground; step time (measured in seconds), which is the time between the heel contact of one side of the body and the heel contact of the opposite side; stride time (measured in seconds), which is the time taken for the left and right limbs to complete one stride; step cadence which is the number of steps taken per minute, and velocity (measured in kilometers per hour), which is the speed of gait [12,16,35]. A blueprint or scan of the feet will also be performed. Having determined the correct shoe size, a trial insole will be made to fit the diagnosis. Further corrections can be made if the desired gait pattern has not yet been achieved. In most cases, the insole’s influence should be directly recognizable after a couple of steps. The insoles will be designed for both injured and non-injured side based on patients’ specific needs. The movement cycles can be recorded with patients going barefoot, wearing shoes, or foot orthoses [36]. The carbon element that stiffens the orthosis is narrow, while the cover is wide, allowing for optimal fitting in various shoes without causing damage to the carbon [35], so that patients can wear them every day regardless of the type of footwear used and the type of activity undertaken.

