#### 2.4.1. Gait Analysis

During gait analysis, the patient will be asked to stand upright on the Scheinworks treadmill (Model FDM-TDSL-3i). Initially, a static measurement of plantar pressure will be taken. Before starting their treadmill exercise, the participants will receive a safety briefing and a 3 min familiarization period for walking. Then, patient will begin walking on the treadmill while dynamic measurements are recorded. The treadmill features a plantar pressure measuring plate integrated underneath it, which has capacitive sensors to measure the distribution of plantar pressure not only during orthostasis but also during walking. The sensor plate integrated into the treadmill offers analysis of the pressure, power, time, and step parameters and evaluation of gait symmetry as standard [12,35,40]. The pressure plate has a sensing area of 94.8 × 40.6 cm and incorporates 5376 capacitive sensors, with a resolution of 1.4 sensors/cm^2^, a measurement area of 1–120 N/cm^2^, and precision of ±5% of the final value. The treadmill has a contact surface of 200 × 92 cm and its belt speed can be adjusted between 0.2 and 24 km/h in 0.1 km/h steps [35]. Before the baseline assessment, the patients will be given a trial using the platform to become familiar with the test method. During this examination, the participants will walk barefoot, while the platform will be calibrated before each attempt. Each patient will be asked to perform five trials, out of which the average of three good attempts for each evaluated parameter will be considered for analysis. A good attempt is defined as both feet making contact with the platform at least three times during walking, eyes remaining open throughout the test, walking without stopping at the participant’s preferred speed, and an absence of excessive trunk rotation [12,40,41].

During these analyses, the data interpretation will occur directly after the measurement. The software will be used to calculate spatial and temporal gait parameters and to analyze the data. The results will then be immediately available in the form of a report.

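### Patients are randomised before the baseline assessment although the design does not need that order; measure baseline first, then release the allocation and fit the insoles

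*Protocol article*

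**What the plan says.** On the order of events, section 2.2.4 (Interventions) opens with "Before the baseline assessment, patients will be divided into two groups". Section 2 (Materials and Methods) describes that division as random allocation, done "using a system of random number tables by one investigator who will not be involved in the recruitment process and data collection".

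On the insoles, section 2.2.4 says Group 1's orthoses are "specially designed to correct the asymmetries detected on the first set of measurements". The asymmetries are found on the treadmill: "The Scheinworks treadmill will be used for this purpose, allowing a practical equilateral overview of important gait parameters". Section 2.4.1 (Gait Analysis) uses the same treadmill for the gait outcomes. A trial insole is then made, and "Further corrections can be made if the desired gait pattern has not yet been achieved". Section 2.2.4 adds: "The movement cycles can be recorded with patients going barefoot, wearing shoes, or foot orthoses".

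On blinding, section 2 states: "The investigators who are involved in data analysis, baseline, and follow-up assessments will be blinded to group allocation".

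On the use of baseline, Study Objectives and section 2.4 (Measurements) both describe comparisons of results before and after the programme.

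**The concern.** Baseline should be fixed before anything about the arm can influence it. Here it is taken after randomisation, for no reason that the design supplies.

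Patients will know whether they are getting insoles, and several baseline tests depend on what they choose to do: pushing against a hand-held dynamometer (2.4.3), walking at their own pace (2.4.1) and holding a single-leg stance (2.4.4). A patient who knows the arm may try harder, or less hard, on these. Myotonometry (2.4.2) is a device reading taken mostly at rest and is much less exposed.

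Two things are at stake. A baseline that differs between arms because of the allocation would pass into any change-from-baseline or baseline-adjusted comparison. And a patient who leaves after allocation but before baseline is a randomised patient without any outcome measurement.

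A smaller, related matter is that one treadmill serves both insole design and outcome measurement, and the article does not say that different people do the two jobs.

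**Working it through.** The plan gives no figure on this point to reproduce. The check compares the stated steps and then works out an illustrative size.

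**Step 1: is baseline after randomisation?** Section 2.2.4 puts the division into groups before baseline. Section 2 makes that division the random allocation. So yes, as written.

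**Step 2: does the design need that order?** Insole design needs the first measurements as input. The first measurements need nothing from the allocation, since both arms have the same tests. The dependence runs from measurement to insole, so measuring before allocating costs no information.

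**Step 3: can fitting disturb baseline?** Trial insoles and corrections come after the measurements they are built from. They cannot change the baseline values. The only route to a biased baseline is knowledge of the arm while the tests are done.

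**Step 4: illustrative size.** Inputs:
- Shift δ in one arm's baseline mean caused by knowing the arm: 0.1 to 0.3 SD. This is an assumption; the document gives no value. The direction is unknown.
- The shift affects baseline only and does not recur at 3 months (assumption).
- Regression slope b of the 3-month value on baseline, in SD units: 0.5 (assumption).
- Planned effect size 0.8 and total sample 42 (section 2.1).

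Formulas, in absolute size:
- Change score: bias = δ
- ANCOVA: bias = b × δ
- 3-month values alone: bias = 0

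| δ (SD) | Change score | As share of 0.8 | ANCOVA, b = 0.5 | As share of 0.8 |
|---|---|---|---|---|
| 0.1 | 0.1 | 0.1/0.8 = 12.5% | 0.5 × 0.1 = 0.05 | 6.25% |
| 0.2 | 0.2 | 0.2/0.8 = 25% | 0.5 × 0.2 = 0.10 | 12.5% |
| 0.3 | 0.3 | 0.3/0.8 = 37.5% | 0.5 × 0.3 = 0.15 | 18.75% |

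A slope between 0 and 1 puts the ANCOVA bias between that of the 3-month comparison and that of the change score.

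**Step 5: loss before baseline.** Each such patient is 1/42 = 2.4% of the sample. The document gives no basis for predicting how many there would be.

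**Step 6: blinding.** Section 2 promises blinded baseline and follow-up assessors. Section 2.2.4 needs someone who designs and corrects insoles, and that person knows the patient is in Group 1. The two statements are compatible if different people do the work. The article does not say so, although section 2.3 takes care to state that the physical therapist is blind to baseline measurements.

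**The case against.** The strongest reply is that allocating is not the same as disclosing. An investigator outside recruitment and data collection draws the assignment, so it could exist on paper before baseline and be kept from the patient and the assessor until afterwards. The article does not say when patients learn their arm, and the flow chart (Figure 1) is not available here and might settle it. This stands: the bias is conditional on disclosure. It does not justify the order. If the allocation is withheld until after baseline, the article should say so; if Figure 1 shows another order, it must be reconciled with section 2.2.4.

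A reader might infer that blinding is already broken. The documents do not support that. They nowhere say that an outcome assessor designs, fits or re-tests insoles, and a separate fitter working from the treadmill report would satisfy both sections. The outcome gait test is also barefoot (2.4.1), which limits unmasking during the test itself.

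A reader might also infer that extra treadmill walking by Group 1 distorts its baseline. Step 3 rules this out, and the text does not state outright that corrections are made on the treadmill.

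Two further points stand. The article fixes neither a change-score analysis nor ANCOVA, so the table shows what could happen, not what will. And a patient lost before baseline would still have eligibility information and possibly demographic data; only the outcome measurements would be missing.

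**Conclusion.** The point holds for the sequence. By the article's own statements, baseline follows randomisation, the design does not require it, and the planned before-and-after comparisons use that baseline. Whether bias results depends on patients learning their arm before the tests, which is neither stated nor excluded. Its size is unknown. Under the assumed shift of 0.1 to 0.3 SD it would be 0.1 to 0.3 SD for a change score, 0.05 to 0.15 SD for an ANCOVA with slope 0.5, and nil for 3-month values alone. The exposed outcomes are strength, preferred-speed gait and balance, with myotonometry much less so.

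The separation of insole fitting from assessment is a safeguard for the promised blinding; no breach is shown. Overall this is an avoidable risk with a cheap remedy, and the change should be made.

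**What to change.** Rewrite section 2.2.4, and Figure 1 if needed, so that the order is:
1. consent;
2. treadmill familiarisation;
3. all baseline outcome measurements;
4. release of the allocation by the independent investigator;
5. insole fitting for Group 1.

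Add to section 2 or 2.2.4 that insole design and fitting take place after baseline, are done by the insole supplier or other existing staff who are not outcome assessors, and that recordings made during fitting are not outcome data.

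The cost is a reordering of visits and a few sentences. No measurements are added. Group 1 may need a slightly longer or separate fitting appointment.
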